#### Monitoring harms

The purpose of monitoring is to maximize benefit and minimize harm. Patients will be asked to report any experienced adverse events from participating in the intervention. Any events that occur as a result of the activities of the study trial will be registered by the principal investigator (MM). Patients who experience an adverse event will be referred to health personnel for medical assessment. The research group has medical knowledge and knowledge of availablesupport.

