### Randomization and blinding

Individuals meeting the inclusion criteria will be randomized into three groups (two intervention groups and one control group) using the Smart-Trial (S-T) electronic data capture platform hosted by Region Örebro County. Randomization will be performed in a 1:1:1 ratio using a block of 6 (9 or 12 to be determined). Stratification will not be applied. During the clinician-rated assessment interview, participants will be instructed not to disclose their group assignment. Due to the nature of the intervention involving structured physical exercise with or without additional person-centred cognitive skills training, blinding of participants to the interventionists in the planned RCT will not be feasible. The individuals collecting the physical tests will also not be blinded to group allocation. However, the data analysts will be blinded to group allocation during the analysis process.

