**Type of intervention: MEP** – a structured physiotherapy-led exercise programme; or **MEP-C** – MEP together with an occupational therapist-led, person-centered cognitive intervention.**Dose, MEP**: Physical exercise for 45 min, three times a week for 12 weeks. **Dose, MEP-C:** Occupational therapy for 60 min approximately six times (every second week) during the 12-week period depending on participant’s goals related to the intervention; and physical exercise for 45 min, three times a week for 12 weeks.**Dose, MEP**: Physical exercise for 45 min, three times a week for 12 weeks. **Components of physical exercises, MEP and MEP-C**: All exercise sessions will have the same structure and consist of endurance, strength and flexibility training. Desired heart rate (HR) range will be 60–90% of maximum HR. In order to track HR during all sessions, both in the clinic and at home, the participants will have a Polar Heart Rate Monitor, model H10 (Polar Electro Oy, Kempele, Finland), connected to their mobile phone. Each exercise session will start with 5–10 minutes’ **warm-up** on an ergometer or using body movements. Next will be **endurance exercises** in three to five intervals of 1 min work and 1 min active rest between each interval. The **strength training exercises** will consist of five different exercises with 1-minute intervals between exercises, in three rounds. These strength exercises may vary depending on the location, indoors or outdoors. However, they will always include one exercise mainly for leg strength, for example squats or lunges; one exercise for arms and shoulders, for example shoulder press with barbell or bench press; one core exercise, for example crunches or the plank; and one balance challenge, for example standing on one leg. The participants will be encouraged to do as many repetitions as possible in 1 min and therefore the load of the exercise can be altered depending on the number of repetitions the participant can manage. In the cool-down, in the warm-up and during stretching the participant will be encouraged to sense the feeling of the body and their overall feeling.**Components of the cognitive intervention of the MEP-C**: As previously mentioned, the cognitive intervention will be conducted by an occupational therapist on approximately six occasions during the 12-week period. Based on self-prioritized goals concerning structure, planning and organization in everyday life, a treatment plan for cognitive skills training will be drawn up. This will form the basis of the treatment. (Examples of such goals are: to arrive on time for training, or to create the space for physical activity in one’s everyday life through improved time management.)**Sequences**: The training sessions will take place either in the training facilities at the outpatient clinic or outdoors in a nearby park. Each session will follow a specific structure.**Modifications**: Alternative exercises will be suggested by the instructors when needed. Participants will be allowed to perform to the best of their ability, with encouragement from the physiotherapists to use maximum effort.**Selection of instructors**: The instructors for the physical exercise sessions will be licensed physiotherapists at the Unit for Psychiatric Physiotherapy, Region Örebro County, who are experienced in working with persons with ADHD. The instructors for the cognitive intervention will be occupational therapists with experience of both working with persons with ADHD and using the Canadian Occupational Performance Measure (COPM) as person-centred tool [33, 34].**Home practice**: In addition to the physiotherapist-led group, the participants will be expected to exercise individually once a week, to the extent needed to reach 150 minutes’ exercise per week. Participants receiving cognitive skills training will be given home assignments, primarily to implement compensatory cognitive strategies in daily life.**Fidelity**: Training adherence will be noted by the treating physiotherapist and occupational therapist. Group adherence to physical activity will be calculated as the number of patients attending 50% of the sessions. To maintain physical exercise for at least 150 min per week, the HR monitor connected to the participants’ mobile phone will gather the time in an HR zone of > 60%. Attendance rate over the intervention period will be calculated as a mean of the individual percentage.**Control group**: Participants randomized to the control group will continue with their TAU. This will include any ongoing pharmacological and/or non-pharmacological treatment that does not include physical exercise or cognitive skills training during the 12-week period. After the 12-week data collection, the participants will be offered physiotherapy-supported training outside the framework of the study.

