#### Ethics

Participants will receive oral and written information and informed consent will be obtained prior to inclusion. Since people with ADHD have a tendency to act impulsively, willingness to participate in the study will be assessed continuously. The risks of participating in the study are assessed as small. There will be a risk of feeling pain and sustaining injury related to exercise; however, this will be minimized by the fact that a physiotherapist will be present. Also, the programme is structured in such a way as to prevent overexertion and injury. Where participants might experience mental discomfort, support to deal with thoughts and feelings that arise will be available throughout the study. Ethical aspects that will be considered are challenges to personal integrity, confidentiality within the group and handling of negative reactions during assessment or treatment. All data will be anonymized before its use.

Ethical approval has been obtained from the Swedish Ethical Review Authority (EPM) (2020–05641; 2021–02743) and the study will be conducted in accordance with the Helsinki Declaration [65].

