A general challenge in clinical studies is not to have an overwhelming data collection. In the planned RCT the rigorous data collection may be seen as challenging. On the other hand, a well-designed data collection strategy with different types of data and data collection options can be seen as a strength. The data collection with recurrent physical meetings in well-known facilities can ensure successful collection of data, and the collectors can catch up on missing data. Data-driven collections are easily performed on the one hand, but, as seen in our pilot study, they can also be a challenge for some participants [26]. Self-administration in data collections including the level of daily physical activity using an accelerometer as well as an HR monitor may also be a challenge. However, in our pilot study both self-administration and data-driven reporting of daily physical activity using an accelerometer and HR monitor were high, as was adherence to data collection stipulations.

In the planned RCT, participants randomized to the control group will be offered physiotherapy-supported training after the 12-week intervention period. This has both advantages and disadvantages. The positive effects of physical activity are well known and therefore it is considered unethical to not allow physical activity until the long-term follow-up has been completed. In our pilot study very few participants from the control group started physiotherapy-supported training after the 12-week period had ended. However, in the planned RCT study, participants in the control group who will start the physiotherapy-led intervention will not be included in the long-term follow-up and will be considered internal dropouts.

Another weakness of the planned RCT study is that the participants cannot be blinded to the treatment allocation regardless of which group they are in. This may create a conscious or unconscious expectation bias, which was also seen in the pilot study [26]. This is a major and insurmountable problem in the design, which is often seen in training intervention studies [66]. Another challenge is that participants may, during clinician-rated assessments, spontaneously and inadvertently mention the type of intervention they have received.

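### Adverse events are solicited and registered by attributed cause, so the counts cannot be compared with treatment as usual (TAU) and the direction of bias is unknown

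*Protocol article*

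**What the plan says.** Three sentences under Monitoring harms in the protocol article govern adverse events.

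- **Solicitation:** "Patients will be asked to report any experienced adverse events from participating in the intervention".
- **Registration:** "Any events that occur as a result of the activities of the study trial will be registered by the principal investigator".
- **Referral:** "Patients who experience an adverse event will be referred to health personnel for medical assessment". This has no causal limit, but no recording is attached to it.

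No other section provides for recording adverse events whatever their cause, or by the same method in all three arms.

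The comparator is described under the START intervention programme: "Participants randomized to the control group will continue with their TAU". On blinding, the Discussion concedes that "participants cannot be blinded to the treatment allocation regardless of which group they are in". Randomization and blinding states that "the data analysts will be blinded to group allocation during the analysis process", which concerns a stage after events have been registered or not. The Ethics section expects some harm from exercise: "There will be a risk of feeling pain and sustaining injury related to exercise".

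**The concern.** Harms are filtered by cause at two points, when patients are asked and when events are registered. A cause-based filter cannot act alike in arms that differ in whether there is an intervention to blame. Pain, injury or worsening that would have happened anyway has almost no route into the adverse-event data under TAU. In the exercise arms the same event may or may not be registered, depending on whether it is put down to the programme.

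That attribution is made in an open-label setting. The Discussion already accepts that unblinded participants may bring expectation bias to the outcomes, and attribution of harm is open to the same influence. Part of the exercise is done without a physiotherapist present: one individual session a week, plus missed sessions made up at home. Events there depend most on self-report.

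At stake is whether the report can say anything about the harms of exercise relative to usual care. The Rationale hopes START will become an additional treatment option, so readers will look for that statement. An analysis plan cannot repair the gap, because an event that was never registered cannot be analysed.

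**Working it through.** The article states no event rate, safety endpoint or safety sample size, so there is no figure to reproduce. The check sets the rules side by side and then illustrates their effect.

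**Step 1: routes into the adverse-event data.**

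| Event | Exercise arms | TAU |
|---|---|---|
| Attributed to the intervention | Solicited and registered | Cannot arise |
| Attributed to a trial assessment (e.g. submaximal exercise test, MRI) | Registered | Registered |
| Background event, not attributed to the trial | No stated route | No stated route |
| Background event wrongly attributed to exercise | Registered | Cannot arise |
| True exercise harm judged unrelated | No stated route | Cannot arise |

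The arms differ in the first row and the last two. The last two are attribution errors, and they act in opposite directions.

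**Step 2: formula.** Let b be the background event rate in every arm, e the true excess from exercise, s the share of background events in the exercise arms attributed to exercise, and r the share of the true excess attributed to it. Assume assessment-related events are registered equally in all arms, so that they cancel. Then

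registered difference (exercise minus TAU) = r × e + s × b, whereas the true difference is e.

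**Step 3: numbers.** The group sizes come from the Design section: 40 per group, so 80 exercise and 40 TAU. All rates are assumptions.

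- *No true excess, b = 10%, s = 50%:* the registered difference is 0.5 × 10% = 5 points. In counts, 80 × 5% = 4 exercise participants are registered and none under TAU. The true numbers with an event are 80 × 10% = 8 and 40 × 10% = 4.
- *No true excess, low end (b = 5%, s = 25%):* 0.25 × 5% = 1.25 points.
- *No true excess, high end (b = 20%, s = 100%):* 1.0 × 20% = 20 points.
- *True excess e = 10%, r = 50%, s = 0:* the registered difference is 0.5 × 10% = 5 points, half the true excess.

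A registered difference of 5 points is thus compatible with no true harm and with a true excess of 10 points. The data as collected could not tell these apart.

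**Step 4: what all-cause capture would give.** With 80 against 40 participants, the 95% half-width for a risk difference is 1.96 × √(p₁(1 − p₁)/80 + p₀(1 − p₀)/40). For 20% v 10% this is 1.96 × √(0.00200 + 0.00225) = 12.8 points. For 20% v 20% it is 1.96 × √(0.002 + 0.004) = 15.2 points. The comparison would be imprecise, but no longer distorted by the registration rule.

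**The case against.** The strongest case against the point is that the article never says other events are excluded. The section is a few sentences long, and event definitions, forms and relatedness procedures usually sit in a fuller document. No comparative safety endpoint is planned, and the stated purpose of monitoring is to protect participants. Part of this stands: exclusion is inferred. But the registration sentence is the only such rule given, and the solicitation sentence carries the same limit. The finding rests on what these sentences say rather than on missing detail. The absence of a safety endpoint keeps the point modest without removing it.

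Several stronger readings are tempting and are not supported:

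- *Worsening goes wholly unrecorded.* Table 3 schedules the MADRS-S, CGI scales, ISI and EQ-5D-5L without restriction to an arm, and these pick up worsening mood, sleep and pain. Health care use and sick leave are also collected, for costing. These are indirect signals: they are not adverse-event capture, and the scales do not record injuries.
- *TAU can register no events at all.* The rule covers trial activities, and TAU participants undergo the exercise test and, in a subset, MRI. Such events could be registered, but they give no background rate.
- *The participant and an unblinded investigator must both attribute the event.* The article does not say who judges causality or whether the principal investigator knows the allocation. What it supports is that participants know their arm.
- *Exercise will look worse than it is.* The last illustration shows the opposite is equally possible.

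**Conclusion.** The point holds in a limited form. As stated, the rule yields attributed events only. The counts cannot be compared with TAU, and the sign of the error is unknown. Under the assumed rates, with no true excess, the artefact ranges from about 1 to 20 percentage points. The true size cannot be estimated from the article. The conclusion assumes that the registration sentence is the operative rule and that no fuller document provides all-cause capture in every arm. No planned efficacy analysis is affected. The loss is confined to what can be said about harms, which makes this a worthwhile, inexpensive improvement rather than a threat to the primary result.

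**What to change.** Put the same short adverse-event question, worded without reference to cause, to all three arms at weeks 3, 6, 9 and 12. Self-report forms such as the ISI are already scheduled at each of these points. They also fall before control participants are offered supported training, so the arms still differ as randomized. Register every event whatever its cause, keep relatedness as a separate field, and report counts by arm with both all-cause and related totals.

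For participants already past week 12, state in the report that registered harms are attributed events only and do not support a comparison with TAU.

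The cost is one added form in the data capture platform, with a paper version for those who use paper. Questionnaire burden rises slightly, which matters because the Discussion already worries about overloading participants, and more unrelated events will have to be listed. Data collection began in March 2021, so coverage will be partial. All-cause and attributed-only periods should be tabulated separately.

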#### Data storage

The S-T electronic data capture platform will be used. The S-T is a secure system and the content is tailored for this trial with web-based forms for each data collection point to facilitate, store and monitor outcomes. The platform is provided by RÖL and the security of the system is based on the rules and regulations concerning sensitive data. To log in as a researcher to all levels of the system, two-step verification is needed. For the participants, one-step verification is needed to register their answers. All communication with the database is encrypted and back-up is done regularly to secure data. Moreover, there is automatic marking of the event when data are missing or entered inaccurately.

It will be possible to efficiently follow each participant throughout the trial, and the data will be organized by unit. The system will therefore give a clear visual overview of each participant’s status. The use of the S-T fulfils the requirements of the European General Data Protection Regulation (GDPR). Only parts of the research group will have access to the S-T. For a researcher to gain access to the system, the principal investigator (MM) will have to approve this action, and will also have to determine what role the researcher who will be gaining access will have (e.g. entering or viewing data).

Directly after inclusion, participants will be registered in the S-T with their participant code and randomized to an intervention allocation. Raw data from physical data collection will be collected on paper forms, one bundle for each data collection point, containing all measures applicable to the specific occasion. The forms in the bundles will be in their original formats and will not have been changed by the research group. Once the data collection is completed and all raw data have been entered into the S-T, the data will be exported to statistical software for further analysis.

#### Ethics

Participants will receive oral and written information and informed consent will be obtained prior to inclusion. Since people with ADHD have a tendency to act impulsively, willingness to participate in the study will be assessed continuously. The risks of participating in the study are assessed as small. There will be a risk of feeling pain and sustaining injury related to exercise; however, this will be minimized by the fact that a physiotherapist will be present. Also, the programme is structured in such a way as to prevent overexertion and injury. Where participants might experience mental discomfort, support to deal with thoughts and feelings that arise will be available throughout the study. Ethical aspects that will be considered are challenges to personal integrity, confidentiality within the group and handling of negative reactions during assessment or treatment. All data will be anonymized before its use.

Ethical approval has been obtained from the Swedish Ethical Review Authority (EPM) (2020–05641; 2021–02743) and the study will be conducted in accordance with the Helsinki Declaration [65].

#### Approval and registration

The study has been approved by the Swedish Ethical Review Authority (No. 2020–05641 and 2021–02743 and 2022-03826-02), and is registered with ClinicalTrials.gov (NCT05049239). Any protocol modifications will be communicated to relevant parties.

## Discussion

This article presents a planned RCT to investigate whether a 12-week structured MEP with or without a cognitive intervention including cognitive skills training has an effect on core symptoms of ADHD in adults, as well as on physical, cognitive and mental function and everyday functioning compared with TAU.

The goal of the START intervention is to create evidence for a multimodal, non-pharmacological treatment for adults living with ADHD. Clinical studies in general face several challenges, such as the quality of the outcome measures used, as well as adherence to the intervention, and data collection [66]. In the planned RCT, adherence to the protocol and data collection may be especially challenging because of the symptomatology of adults with ADHD, such as difficulties in managing their time and planning and structuring their everyday life. To maximize adherence to the study protocol, different options will be suggested if participants miss a planned session. A minimum participation level of 50% will be set for the intervention group and participants missing a session will be offered an intervention session on another day of the same week or to catch up the planned exercise session at home and monitor and report their level of activity [26].

The START intervention may contribute to symptom reduction, a healthier and more active life, increased QoL, body experiences during exercise and better everyday functioning. Because of the complexity of the potential outcomes, many different measurements are needed to evaluate progress.

A general challenge in clinical studies is not to have an overwhelming data collection. In the planned RCT the rigorous data collection may be seen as challenging. On the other hand, a well-designed data collection strategy with different types of data and data collection options can be seen as a strength. The data collection with recurrent physical meetings in well-known facilities can ensure successful collection of data, and the collectors can catch up on missing data. Data-driven collections are easily performed on the one hand, but, as seen in our pilot study, they can also be a challenge for some participants [26]. Self-administration in data collections including the level of daily physical activity using an accelerometer as well as an HR monitor may also be a challenge. However, in our pilot study both self-administration and data-driven reporting of daily physical activity using an accelerometer and HR monitor were high, as was adherence to data collection stipulations.

In the planned RCT, participants randomized to the control group will be offered physiotherapy-supported training after the 12-week intervention period. This has both advantages and disadvantages. The positive effects of physical activity are well known and therefore it is considered unethical to not allow physical activity until the long-term follow-up has been completed. In our pilot study very few participants from the control group started physiotherapy-supported training after the 12-week period had ended. However, in the planned RCT study, participants in the control group who will start the physiotherapy-led intervention will not be included in the long-term follow-up and will be considered internal dropouts.

Another weakness of the planned RCT study is that the participants cannot be blinded to the treatment allocation regardless of which group they are in. This may create a conscious or unconscious expectation bias, which was also seen in the pilot study [26]. This is a major and insurmountable problem in the design, which is often seen in training intervention studies [66]. Another challenge is that participants may, during clinician-rated assessments, spontaneously and inadvertently mention the type of intervention they have received.

To gain knowledge of the participants’ own perspectives of the intervention and its eventual benefits, a qualitative study will be performed as part of the planned RCT study. To perform qualitative studies alongside RCT studies is recommended in complex health interventions such as START [67] as it can deepen the understanding of the other outcomes as well as add new research questions.

The potential personal gains from participating in the intervention, alongside the hypothesized health effects and increases in activity, include an easy-to-adopt new lifestyle that can, if implemented regularly, have several positive physical and mental effects. We therefore hope that the knowledge gained from this study will contribute to developing effective long-term strategies to reduce core symptoms and improve QoL for adult patients with ADHD.

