### Sample size estimation

The power calculation is based on the primary outcome, ADHD symptom reduction assessed using the World Health Organization (WHO) Adult ADHD Self-Report Scale (ASRS-v1.1) [32]. Postulating a mean difference in symptom reduction of 15% between the intervention and control groups, with 10.63% SD, 0.05 alpha, 0.8 power and expecting a 25% drop-out, gives a sample size of 120 participants. The actual sample size required for a power of 0.8 is 90 (= 120–120*25%). In case we have larger than 25% drop-out, we will recruit more participants to maintain the necessary power of 0.8.

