
### Data collection

Data will be collected before the intervention, during the intervention at week 3, 6 and 9, and directly after the 12-week intervention. Follow-up assessments will be at 6 and 12 months after the start of the intervention. One month after completion of the intervention, a consecutive sample from each of the two intervention groups (n = 15) will be interviewed regarding their experiences of the intervention and eventual benefits.

All online self-assessment scales will be completed digitally in the S-T electronic data capture platform. The data system will automatically send e-mails to participants informing them to log on to the portal to complete the questionnaires, and will notify them when an assessment is approaching or if a questionnaire has not been completed. Notifications will also be sent by e-mail if questionnaires are not completed within the set time frame. Participants who prefer paper questionnaires will have them sent by post together with an envelope with prepaid postage, and questionnaires will be stored in a locked facility at the University Health Care Research Centre at Örebro, to which only the research team will have access. Physical examinations and magnetic resonance imaging (MRI) examinations will be performed during visits to the outpatient clinic and X-ray clinic, respectively.

Data will be collected both in paper and digital formats and stored in locked fireproof cabinets when not being processed, or on a password-protected server within Region Örebro County (RÖL). The material collected will be provided with a code in place of personal data, and only authorized persons will have access to the code key and materials.

Only authorized project members will have access to all folders and subfolders. The principal investigator (MM) and data handlers will have authorization to read and write in the files under project documents, original data, and personal codes. Collected data will be stored in accordance with current legislation and local guidelines for at least 10 years after publication. All project data will be stored on the server, which can only be accessed at RÖL or via a virtual private network (VPN) or, outside RÖL’s area, with a password to the computer and VPN.

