### Analysis

#### Analysis of quantitative data

Descriptive analysis will be performed and the results will be reported using means ± standard deviations and ranges for continuous variables and numbers and percentages for categorical variables. Data will be analysed with a modified intention-to-treat (ITT) method and all patients involved in at least one data collection will be included in the analysis. Missing values will be imputed with multiple imputation method. Per-protocol (PP) analysis will also be performed where relevant. Analysis of variance (ANOVA) will be performed to compare means of the groups. The differences in baseline characteristics and post-intervention changes between the groups will be tested using *t*-test, Mann-Whitney U test, or Chi-squared test, whichever is appropriate. All analyses will be performed in the statistical software SPSS version 25.0 (IBM Corp., Armonk, NY, US).

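### Ending 6- and 12-month follow-up for control participants who take up the training offered after week 12 is a one-arm, post-randomisation exclusion that may bias the long-term comparisons with TAU

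*Protocol article*

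**What the plan says.** In the protocol article, the control-group paragraph of the section on the START intervention programme reads: "After the 12-week data collection, the participants will be offered physiotherapy-supported training outside the framework of the study". The Discussion adds that control participants who start this training "will not be included in the long-term follow-up and will be considered internal dropouts". No matching rule exists for MEP or MEP-C participants, whatever they do after week 12.

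The section on analysis of quantitative data sets a modified ITT approach in which "all patients involved in at least one data collection will be included in the analysis", with multiple imputation of missing values.

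The affected time points matter to the trial. The Data collection section states: "Follow-up assessments will be at 6 and 12 months after the start of the intervention". Table 3 schedules ASRS-v1.1, CGI-S, CGI-I and EQ-5D-5L at both, and the Abstract lists both as times at which the effect is measured. The health economic section plans a 1-year cost–utility analysis against the control group.

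The Discussion gives an ethical reason for the offer, grants that it has drawbacks, and reports that few pilot controls took it up. It does not name the exclusion as a source of bias, and it does not relate it to the modified ITT set.

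**The concern.** Randomisation protects a comparison only if everyone randomised is followed, or if losses are unrelated to outcome. Here one arm loses participants because of something they choose to do after week 12, and nobody in the other two arms can be lost for that reason. If controls who start training would have fared differently at 6 or 12 months from those who do not, the remaining controls no longer represent the arm as randomised.

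At stake are the comparisons with TAU on ADHD symptoms at 6 and 12 months, and QALYs and costs over one year. The protocol also leaves open whether an internal dropout is left out of the analysis or imputed. The two treatments answer different questions. Outcomes that are never collected cannot be recovered when the analysis is written.

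**Working it through.** **1. The plan's own figures.** Sample size estimation takes 15% as the target difference in symptom reduction. Its remaining inputs read: "with 10.63% SD, 0.05 alpha, 0.8 power and expecting a 25% drop-out, gives a sample size of 120 participants".
- The dropout step reproduces. The article puts the evaluable number this way: "The actual sample size required for a power of 0.8 is 90". Then 90 / (1 − 0.25) = 120. With 1:1:1 allocation this is 40 randomised and 30 evaluable per arm.
- The 90 does not follow from the stated effect and SD. A two-sided comparison of two means needs 2 × (1.96 + 0.84)² × (10.63/15)² ≈ 7.9, so 8 per arm. That is a separate matter and is not used against the plan here.
- Planned standardised effect: 15 / 10.63 = 1.41 SD.

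**2. The two readings of internal dropout.** Every control who starts training was randomised and has data from before the offer, so the modified ITT set includes them.
- *Deleted:* the Discussion contradicts the analysis section.
- *Imputed:* the two sections are compatible. The 6- and 12-month values are then predicted from observed data (ASRS at baseline, week 6 and week 12) under a missing-at-random assumption. The result estimates the contrast with controls had none of them taken up training. The effect as randomised cannot be estimated, because the data for it were not collected.

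**3. Size under deletion.** Let a share p of controls leave, and let leavers differ from stayers by delta SD. The full control mean is the stayers' mean plus p × delta, so deletion shifts the control mean by p × delta. Neither p nor delta is in the protocol; both are assumptions. Points are percentage points of symptom reduction at SD 10.63.

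| p | delta | shift (SD) | shift (points) | share of 1.41 SD |
|---|---|---|---|---|
| any | 0 | 0 | 0 | 0% |
| 10% | 0.3 | 0.03 | 0.32 | 2% |
| 30% | 0.5 | 0.15 | 1.59 | 11% |

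**4. Cross-check.** Take a normal model in which uptake propensity correlates rho with outcome. The shift is rho × φ(z)/(1 − p) × 10.63, with z the (1 − p) normal quantile. For p = 30% and rho = 0.3: 0.3 × 0.3477/0.7 × 10.63 = 1.58 points, matching the last row above. With 30 per arm and no true effect, type I error is 0.075 (simulated) to 0.08 (calculated) under deletion, against about 0.05 if all controls are followed. With rho = 0 the simulated bias is about zero.

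**5. Precision.** If leavers come on top of the 25% dropout, 30 controls become 27 (p = 10%) or 21 (p = 30%). Power for the planned 15-point difference against 30 in an exercise arm stays at 0.999 and 0.998. If leavers fall within the 25%, nothing further is lost.

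**The case against.** The strongest reply is that the rule and the modified ITT statement can live together. Internal dropouts have earlier data, stay in the analysis set and are imputed. Bias is then only what remains after conditioning on their earlier scores, and the shifts above, which assume deletion, do not apply. This stands as a possible reading, and the documents do not allow that remaining bias to be computed. It does not remove the problem: outcomes that could be collected are given up, and only the effect without uptake can be estimated.

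Pilot uptake was low, which also stands, but only five participants were randomised to control there. That cannot bound uptake among 40. If uptake is indeed rare, following these few people costs very little.

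The plan promises further recruitment if dropout exceeds 25%. That answers loss of numbers, not selection. Health-care costs come from administrative systems or medical records and need not be lost with the visits; EQ-5D-5L would be.

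A reader might infer that every long-term comparison is biased, that ITT is certainly broken, or that uptake is driven by symptoms and motivation. The documents support none of these. MEP versus MEP-C does not involve controls. The ITT conflict arises only under deletion. Nothing says who accepts the offer. Nor do the documents support large shifts: 50% uptake with a 0.8 SD difference would give 0.40 SD, but no figure in the protocol points to such values.

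**Conclusion.** The point holds in limited form. The Discussion fixes a one-arm exclusion, triggered after randomisation, that may bias the comparisons with TAU at 6 and 12 months and the 1-year cost–utility analysis. Week 12 precedes the offer, so the post-intervention results and the 3-month cost–utility analysis stand.

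Direction is unknown. Bias is zero if uptake is unrelated to prognosis. Under deletion it is 0.03 to 0.15 SD for assumed uptake of 10% to 30% and assumed differences of 0.3 to 0.5 SD, taking the planning SD to apply at the later visits. The upper value is about a tenth of the planned effect, and it would weigh more if the true long-term effect is smaller than planned. Power for the planned effect is not the issue. The defect is that, under either reading, the long-term effect as randomised cannot be estimated.

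**What to change.** - Leave the training offer as it is and delete the sentence that ends follow-up for those who accept it.
- Collect the scheduled 6- and 12-month outcomes (ASRS-v1.1, CGI-S, CGI-I, EQ-5D-5L) and costs from all randomised controls. Record whether and when each started the training.
- Analyse all participants as randomised, so that the Discussion and the modified ITT statement agree. The long-term contrast is then START versus TAU followed by an offer of training.
- Add a supplementary analysis that sets control data after uptake to missing and imputes them from controls who did not take up training, labelled as the effect without uptake.
- Data collection began in March 2021, so some visits may already have been skipped under the rule. Report these as missing, with the reason.

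The cost is a change of wording and attendance at visits already in the schedule. The downside is that uptake may dilute the as-randomised long-term effect; the supplementary analysis shows how much this matters under its assumption.
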